### De-implementation strategy

The process to tailor the de-implementation of unnecessary antibiotic prescriptions will combine multifaceted interventions which include health worker education, organizational adjustments, audit and feedback, and roll-out of the CDSA (Table 1). We will start the intervention period by holding an educational meeting with clinicians from the three intervention sites about the de-implementation of unnecessary antibiotic prescriptions to treat URTI as indicated in the CDSA. During the meeting, we will explain to the prescribers how to use the CDSA. In this meeting, we will distribute the CDSA to each participant. In addition, CDSAs will be posted on either the exam room wall or on the clinician´s exam room desk for ease of reference during clinical visits. Further, based on the results of our baseline assessment about potential barriers and facilitators to the use of our CDSA, we will work with the facility to make any organizational adjustments that may be necessary to address potential barriers. In each participating facility, we will identify one local coordinator who will function as a local champion for this intervention, be responsible for the enrollment of participants and obtaining informed consent from potential trial participants or surrogates, and serve as the study focal point for coordination with the study researchers. Finally, throughout the implementation phase, the study researchers will conduct a prescription audit and feedback on 50% of the antibiotic prescriptions that were made during this period. They will then meet with intervention site clinicians, every other week, to review the audit findings and provide feedback as to maximizing the use of the CDSA.

**Table 1 Tab1:** Summary of de-implementation strategy

Item	Description
Education	Educate clinicians in using the CDSA highlighting the de-implementation of unnecessary antibiotic prescriptions to treat URTI
Organizational adjustments	We will adjust the workflow based on the local setting to fit the intervention
Audit and feedback	Some prescriptions will be audited in the clinical sessions and feedback will be given. Once in two weeks, the principal investigator will meet the local coordinator or champion to monitor and evaluate the records and feedback will be given to improve the implementation of the intervention
Roll-out the CDSA	A4 poster with the algorithm to support clinical decisions will be posted on the wall of the consultation room or placed on the table

### Data collection and measures

Phase one (Pre-implementation)

Data for the study will be drawn from multiple sources. For phase one, we will collect qualitative data about the current context of both intervention and control sites regarding the treatment of URTI among outpatient HIV-infected patients. We will conduct in-depth interviews among relevant healthcare workers which will include clinicians, pharmacists, and laboratory technicians using interview forms to guide and collect data. Interviews will include a combination of close-ended and open-ended questionnaires to explore current antibiotics prescribing practices for URTI, current workflow of patients through the facility, management of work processes, existence of current practices and normative documents in performing prescription audits and feedback, existence of any initiatives for implementing an antimicrobial stewardship program (ASP), willingness to work as a team to change work processes, availability of medicines to treat URTI, and current laboratory capacity for diagnosing the etiology or a URTI.

Phase two (adaptation and implementation) and phase three (post-implementation)

Throughout phases two and three we will collect both quantitative and qualitative data. For each HIV-infected patient determined to be eligible for this study, we will collect information related to their socio-demographics, current symptoms, and management decisions related to antibiotics. If antibiotics are prescribed, we will collect data on the type of antibiotic, and expected length of treatment. Antibiotic prescriptions data will be collected from both pharmacy and medical records. To assess whether a clinician has adopted the de-implementation of unnecessary antibiotic use, the duration of symptoms and prescriptions will be reviewed in the clinical records. This will be measured as the proportion of clinicians who adopted the de-implementation of unnecessary antibiotic use practices among those who participated in the study. The “Reach” outcome will be measured as the proportion of patients in the target population reached by the intervention (in terms of # patients recruited, # patients refused and # patients recruited and dropped out during the intervention). This data will be collected from the study data record form.

Qualitative data will be collected to measure the satisfaction of health workers regarding the implementation of the intervention including information related to adoption and acceptability of the intervention. This data will be collected through in-depth interviews with intervention site clinicians, using an interview guide and will be audio recorded. The interview guide will contain open-ended questions related to the adoption, fidelity, and acceptability of the intervention. An additional survey will be used to assess the degree of clinicians’ satisfaction. Maintenance will be measured as both the number of sites and clinicians that maintain the use of the de-implementation strategy one year after completion of the intervention implementation. This data will be collected from prescriptions and clinical records.

Secondary outcomes consist of the incidence of complications as a result of non-prescription of an antibiotic and the mean time for complete recovery from the first medical visit. This information will be collected from the study data record form. The incidence of complications will be measured as the proportion of complications arising from non-prescription of an antibiotic among patients who did not receive antibiotics. The mean time for complete recovery will be measured as the average time that the patients took to recover completely from their symptoms.

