**Methods:**

This study is a multicenter, two-arm, cluster randomized controlled trial, involving six primary health care facilities in Maputo and Matola municipalities in Mozambique, guided by an innovative implementation science framework, the Dynamic Adaption Process. In total, 380 HIV-infected patients with URTI symptoms will be enrolled, with 190 patients assigned to both the intervention and control arms. For intervention sites, the CDSAs will be posted on either the exam room wall or on the clinician´s exam room desk for ease of reference during clinical visits. Our sample size is powered to detect a reduction in antibiotic use by 15%. We will evaluate the effectiveness and implementation outcomes and examine the effect of multi-level (sites and patients) factors in promoting the de-implementation of unnecessary antibiotic prescriptions. The effectiveness and implementation of our antibiotic de-implementation strategy are the primary outcomes, whereas the clinical endpoints are the secondary outcomes.

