### Study design and conceptual frameworks

We propose a multicenter two-arm cluster randomized controlled trial that will employ a mixed-methods approach. This study will be guided by two conceptual frameworks, the Dynamic Adaptation Process (DAP) and the Reach, Effectiveness, Adoption, Implementation, and Maintenance (RE-AIM) framework, and will be carried out in three phases (Fig. 1). The DAP framework was developed to provide the structure for an iterative process to guide, monitor, and evaluate the introduction of a new intervention into practice. DAP is a framework that allows changes to be made according to the real context by the possibility of tailoring the elements of the intervention based on data obtained during the pre-implementation and the adaptation. DAP engages stakeholders at all levels to develop robust implementation strategies and will guide the work of phases one, two, and three in our study [29]. *Phase one* (pre-implementation) will consist of a formative baseline evaluation of the current situation for antibiotic prescribing for URTI in the outpatient setting among PLHIV and occur over three months. It will consist of interviews with identified health workers to understand the current antibiotic prescribing practices for URTI among HIV-infected ambulatory patients, as well as perceived facilitators and barriers to the roll-out of our de-implementation strategy. A document review will be performed to identify the existence of national guidelines or normative documents driving antibiotic prescribing for URTI. Phase one will also include documentation of current laboratory diagnostic capacity for URTI and a situational assessment of the availability of medicines to treat URTI. *Phase two* (adaptation and implementation) consists of our de-implementation strategy roll-out and will occur over six months. Based on information learned in phase one, we will make workflow adjustments to address realities on the ground. The CDSA will be rolled out within a two-arm cluster randomized control trial design in which our primary outcome measure will be the clinical decision to use antibiotics or not. Intervention elements and study tools will be adapted before the intervention is implemented. Throughout this phase, an implementation audit and continuous feedback will be conducted to guarantee and monitor adherence to the intervention protocol. *Phase three* (post-implementation) will consist of a three-month post-implementation phase in which we will analyze implementation outcomes and processes as a function of the RE-AIM conceptual framework, in real-time. *Reach* will be assessed in terms of patient recruitment, refusal, and attrition. *Effectiveness* will be analyzed by comparing antibiotic use rates and patient-related clinical outcomes between the intervention and control arms. For *adoption*, clinicians who adopted the practice of de-implementation of unnecessary antibiotic use will be assessed using prescriptions and clinical records. For *implementation*, the fidelity and satisfaction of clinicians regarding the intervention will be assessed. For *maintenance*, sites and clinicians that maintain de-implementation practices and use of the CDSA will be assessed one year after completion of the intervention.

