### Intervention and control

Eligible patients allocated to intervention will be managed using the CDSA. Eligible patients are adult HIV-infected with respiratory symptoms (nasal secretions or runny nose, congestion, sore throat, coughing, sneezing, chills, smell and taste disorders, with or without a fever) [30]. Adult HIV-infected patients without URTI symptoms, those with fever ≥ 39ºC, severe mental illness, or advanced HIV status will be excluded from the study. All PLHIV with URTI symptoms lasting less than 10 days will not receive an antibiotic unless there is an additional symptom suggesting a suspect of bacterial infection. Otherwise, bacterial infection will be suspected in the following situations: (i) higher-grade fever than normally observed with the common cold, with the presence of yellow or greenish nasal discharge, pain/difficulty swallowing, or an intense sore throat; (ii) URTI symptoms lasting longer than 10 days; (iii) URTI symptoms continuing to get worse rather than improve over several days (5 days after the first visit) [31].

Decongestants and/or antihistamines may be used to relieve symptoms of cough, congestion, and runny nose at the clinician's discretion [32]. Those with an increase in symptoms after five days, or a persistence of symptoms after 10 days, without systemic symptoms, will be treated with topical nasal steroids. If improvement of symptoms is observed after five days of treatment with nasal steroids, patients will continue with treatment for seven to fourteen days. Without improvement, consider 5 days of treatment with antibiotics. If improvement, patients should continue with treatment for seven to fourteen days. If symptoms get worse after 5 days of antibiotics, patients will be referred to an ear-nose-throat specialist (ENT). On the other hand, those with systemic symptoms without complications will follow five days of treatment with antibiotics, nasal decongestants, and topical nasal steroids (Fig. 3). Those with complications (acute otitis media, sinusitis, bronchitis, and pneumonia) will be given five days of treatment with antibiotics. Then, without improvement after 5 days of antibiotics, patients will be referred to an ear-nose-throat specialist. The promotion of de-implementation of unnecessary antibiotic use for HIV-infected patients with URTI symptoms lasting less than 10 days will be the core strategy of using the CDSA in the experiment arm.

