**Fig. 3 Fig3:**
[figure not shown]
Clinical decision support algorithm

Patients allocated to control will follow usual or routine treatment and will be used as a comparator group. The control arm will allow a fair comparison of the effectiveness of the intervention. No specific intervention will be assigned to the control arm except for follow-up. The clinicians will decide to prescribe medication during each medical visit as they are used to do. For both arms, patients will be enrolled for the first time (t0 = 0 days) and monitored three times (t1 = 5 days, t2 = 10 days, t3 = 15 days) after the initial medical visit to see improvement of symptoms through a phone call, and if necessary, will be asked to visit the healthcare facility for a follow-up clinical examination in person (Fig. 2). If the patient fails to answer the calls at t1, t2, or t3, a home visit on the following day will be made for a follow-up procedure. Participation will be discontinued if the patient’s HIV clinical condition worsens as a result or not of the intervention and appropriate care and treatment will be provided including hospitalization if required.

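### The complication outcome is confined to patients without antibiotics and to complications blamed on non-prescription, so its comparison between arms is not a randomised one

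*Protocol article*

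**What the plan says.** All references are to the protocol article.

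- **Outcome.** Data collection and measures names a secondary outcome, the "incidence of complications as a result of non-prescription of an antibiotic", and defines it as the "proportion of complications arising from non-prescription of an antibiotic among patients who did not receive antibiotics". The only other secondary outcome is mean time to complete recovery, which is not limited to untreated patients.
- **Planned comparison.** Study design and conceptual frameworks says that effectiveness will be analysed by "comparing antibiotic use rates and patient-related clinical outcomes between the intervention and control arms". The Abstract adds that "the clinical endpoints are the secondary outcomes".
- **Primary outcome.** The same design section states that "our primary outcome measure will be the clinical decision to use antibiotics or not".
- **Algorithm.** Intervention and control says: "Those with complications (acute otitis media, sinusitis, bronchitis, and pneumonia) will be given five days of treatment with antibiotics".
- **Follow-up.** The text after Fig. 3 has both arms contacted at days 5, 10 and 15 by telephone, with a home visit if a call is missed. Participation ends if the patient's "HIV clinical condition worsens as a result or not of the intervention".

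**The concern.** The design gives a fair comparison of everyone enrolled at intervention facilities with everyone enrolled at control facilities. The complication outcome drops that comparison in two ways.

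First, its denominator is set by a decision made after randomisation, and that decision is the one the intervention acts on. If the strategy works, more patients go untreated in the intervention arm, and they need not resemble the smaller untreated group in control.

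Second, its numerator needs someone to decide that a given complication arose because no antibiotic was prescribed. That cannot be observed in an individual patient, the article gives no criterion for it, and facility staff know which strategy their site follows.

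At stake is the main harm question of a trial that reduces antibiotic use in people living with HIV and is meant to inform scale-up. Selection could produce a false safety signal or false reassurance, and the outcome as defined gives no way to tell which.

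**Working it through.** The article states no expected complication risk and no sample size for this outcome, so there is no figure to reproduce. The 190 per arm is planned for the primary outcome and is used here only as the full denominator.

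**Inputs**
- 190 patients per arm (Randomization section).
- 0.15 difference in prescribing (Data management and statistical analysis).
- 65.9% prescribing from the investigators' earlier work (Background). It is not stated as a planning rate; using it for control is an assumption.
- 0.659 − 0.15 = 0.509 for intervention, also an assumption.

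**Step 1: denominators**
- Control: 190 × (1 − 0.659) = 64.8, about 65.
- Intervention: 190 × (1 − 0.509) = 93.3, about 93.
- About 66% of control and 51% of intervention patients fall outside the outcome.

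**Step 2: what zero events would exclude**

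The exact upper 97.5% limit is 1 − 0.025^(1/n), ignoring clustering.

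| n | Upper limit |
|---|---|
| 65 (control, as defined) | 5.5% |
| 93 (intervention, as defined) | 3.9% |
| 190 (either arm, all enrolled) | 1.9% |

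With an assumed 5% risk in both arms, the 95% half-width for the difference is 1.96 × √[0.05 × 0.95 × (1/n₀ + 1/n₁)]. That is 6.9 points for 65 v 93 and 4.4 points for 190 v 190, again ignoring clustering.

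**Step 3: selection alone**

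All risks here are assumed. Let 20% of patients be higher risk (15%) and 80% lower risk (2%), with antibiotics having no effect. The true risk is 0.2 × 0.15 + 0.8 × 0.02 = 4.6% in both arms, so the true risk ratio is 1.00. Control prescribes to 95% of higher-risk and 58.6% of lower-risk patients (overall 65.9%). Risk among the untreated in control is then (0.2 × 0.05 × 0.15 + 0.8 × 0.414 × 0.02) / (0.2 × 0.05 + 0.8 × 0.414) = 2.4%. The intervention arm can reach 50.9% in different ways:

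| Prescribing, higher / lower risk | Risk among untreated | Ratio to control |
|---|---|---|
| 95% / 39.9% | 2.3% | 0.95 |
| 75% / 44.9% | 3.3% | 1.40 |
| 55% / 49.9% | 4.4% | 1.84 |

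The restricted outcome thus moves with who is left untreated, even when nothing differs between the arms.

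**Step 4: two readings of non-receipt**

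The definition does not say when receipt is judged. On a first-visit reading, a patient initially untreated who later develops a complication stays in the denominator and is counted if the event is attributed to non-prescription. On an any-time reading, a patient then given antibiotics for that complication leaves the denominator. With an assumed 10% risk among the initially untreated and a share q treated afterwards, the measured rate is 0.10(1 − q) / (1 − 0.10q): 5.3% at q = 0.5, 2.2% at q = 0.8 and 0% at q = 1. The documents do not give q.

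**The case against.** Several points on the other side are fair.

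- **Discontinuation.** A reader might infer that patients who get worse are removed from the trial. The text does not support that. The rule concerns worsening of the HIV condition only. A patient whose respiratory infection worsens stays in the pathway, and nothing says that data collected before discontinuation are discarded. Advanced HIV is an exclusion and follow-up is 15 days, so the documents do not show a material loss.
- **Harms removed by definition.** A reader might also infer that the definition removes most harms, or forces measured incidence towards zero. That needs the any-time reading, which the article does not state. The outcome's name suggests that non-prescription comes first and the complication follows, which fits a first-visit reading better. What stands is that the time of classification is not stated.
- **Size.** The prescribing rates and risks are assumptions, and the shift may be small. If risk rose linearly from 1% to 9% and the lowest-risk patients were the ones left untreated, the untreated risks would be 0.01 + 0.08 × 0.341/2 = 2.4% in control and 0.01 + 0.08 × 0.491/2 = 3.0% in intervention. That 0.6-point gap is well inside the 6.9-point half-width.
- **Other evidence.** Time to recovery is measured without restriction, so clinical outcome is not judged only through complications. It does not count complications, however.
- **Rank.** This is a secondary outcome, and the power calculation does not rest on it.

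None of this restores the randomised comparison. The article states the numerator and denominator outright, so this is not detail left to an analysis plan; a plan that followed the definition would inherit the problem.

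**Conclusion.** The point holds in this form: as defined, the complication outcome conditions on a post-randomisation variable that the intervention is meant to change, requires an unobservable attribution, and leaves out complications in treated patients. It cannot deliver the between-arm comparison that the article plans for clinical outcomes. This conclusion follows from the definition and needs no assumed number.

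The size does rest on assumptions. At 65.9% v 50.9% prescribing, roughly a third of control and half of intervention patients would contribute. The direction and amount of selection bias cannot be derived from the documents; the ratios of 0.95 to 1.84 under no true effect show only that it can go either way. The share of complications lost on the any-time reading cannot be derived either.

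**What to change.** **Change**
- Define the outcome as any listed complication (otitis media, sinusitis, bronchitis, pneumonia) with onset after t0 and by t3, in all enrolled patients by the arm of their facility, whatever antibiotics they received and without attribution of cause.
- Report the risk in each arm and the difference, with a confidence interval that allows for clustering.
- Keep patients whose participation ends because their HIV condition worsens in the analysis, with the outcome data available and, where they agree, continued outcome follow-up. Their care is unaffected.
- Retain the present measure as descriptive only, with non-receipt classified by the first-visit decision.

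**Cost**
- Recruitment began in June 2024, so this is a change to a secondary outcome in a running trial. It should be dated and made before outcome data are analysed.
- The contacts at days 5, 10 and 15 already exist in both arms, but the article describes the calls as checks on symptom improvement. Complications must be recorded in the same way for treated and untreated patients.
- With three facilities per arm, the interval will be wide, and the report should say so.

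### The secondary outcome averages completed recovery times, but no patient contact is described after day 15, so an average of completed times leaves out the slowest recoverers

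*Protocol article*

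**What the plan says.** Under Data collection and measures, the protocol article lists two secondary outcomes. One is "the mean time for complete recovery from the first medical visit", defined as follows: "The mean time for complete recovery will be measured as the average time that the patients took to recover completely from their symptoms". It gives no value for a patient who has not recovered when follow-up ends.

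The schedule is in the section Intervention and control, in the text after Figure 3. In both arms patients are "monitored three times (t1 = 5 days, t2 = 10 days, t3 = 15 days) after the initial medical visit". The purpose of the contact is "to see improvement of symptoms through a phone call, and if necessary, will be asked to visit the healthcare facility". After an unanswered call, "a home visit on the following day will be made for a follow-up procedure". No patient contact after the third is described.

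The same section sets out the algorithm for the intervention arm. Patients with worsening after five days or "persistence of symptoms after 10 days, without systemic symptoms, will be treated with topical nasal steroids". The next step reads: "If improvement of symptoms is observed after five days of treatment with nasal steroids, patients will continue with treatment for seven to fourteen days". Patients who do not improve may move on to five days of antibiotics, and those who then get worse are referred to a specialist.

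**The concern.** The article states both the quantity (a mean of completed times) and the horizon (15 days), and the two do not fit together. A mean time to complete recovery needs a recovery time for every patient, and a patient still ill at the last contact has none. If only completed times are averaged, inclusion depends on the outcome itself, and an arm with slower recovery loses more of its slow patients.

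What is at stake is the clinical comparison. The other secondary outcome, complications, is counted only among patients who received no antibiotic. Time to recovery is therefore the only listed clinical outcome that covers all patients in both arms. If less antibiotic use did lengthen illness, a recovered-only average would tend to shrink the visible difference.

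**Working it through.** **1. Can recovery fall after the last contact?** Take the branch for symptoms that persist after 10 days and count from the first visit.
- Five days of nasal steroids end on day 10 + 5 = 15. A patient who has not improved may then start antibiotics, and is by definition symptomatic at the last contact.
- A patient who has improved continues for 7 to 14 days. This runs to day 22 to 29 if those days are additional, or to day 17 to 24 if they are the total course.
- For a patient who worsens at day 5, steroids run to day 10 and antibiotics, if used, to day 15, where a worse patient is referred.

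If the 10 days count from symptom onset, the dates move earlier by the symptom duration at the first visit. The algorithm therefore allows for patients unrecovered at day 15. It does not say how many.

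**2. Inputs.** From the article: contacts on days 5, 10 and 15, and 190 patients per arm. It gives no mean, SD or share unrecovered for this outcome, so there is no stated figure to reproduce. Assumed: log-normal recovery time with median *m* and log-SD *s*, over a range.

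**3. Formulas**, with cut-off 15 and Φ the standard normal distribution function:
- d = (ln 15 − ln m)/s, and share recovered F = Φ(d)
- P = m·exp(s²/2)·Φ(d − s)
- recovered-only mean = P/F
- restricted mean over 15 days = P + 15(1 − F)

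Example with m = 8, s = 0.6: d = 1.048, F = 0.853, P = 9.578 × 0.673 = 6.444. The recovered-only mean is 6.444/0.853 = 7.56 days, and the restricted mean is 6.444 + 15 × 0.147 = 8.66 days. For m = 10 the two are 8.46 and 10.09 days. The differences are 0.90 and 1.44 days, so the recovered-only difference is 1 − 0.901/1.437 = 37% smaller.

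| Medians (days) | log-SD | Unrecovered at day 15 | Recovered-only difference | Restricted-mean difference | Shortfall |
|---|---|---|---|---|---|
| 4 vs 6 | 0.4 | 0.05% vs 1.1% | 2.05 | 2.14 | 4% |
| 4 vs 6 | 0.6 | 1.4% vs 6.3% | 1.72 | 2.13 | 19% |
| 5 vs 6 | 0.4 | 0.3% vs 1.1% | 1.00 | 1.06 | 6% |
| 5 vs 6 | 0.6 | 3.4% vs 6.3% | 0.80 | 1.03 | 23% |
| 8 vs 10 | 0.6 | 14.7% vs 25.0% | 0.90 | 1.44 | 37% |
| 8 vs 10 | 0.8 | 21.6% vs 30.6% | 0.69 | 1.20 | 43% |
| 9 vs 12 | 0.6 | 19.7% vs 35.5% | 1.08 | 1.80 | 40% |
| 9 vs 12 | 0.8 | 26.2% vs 39.0% | 0.84 | 1.50 | 44% |

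In the 8 vs 10 case with log-SD 0.6, about 28 and 47 of 190 patients per arm (190 × 0.147 and 190 × 0.250) would have no completed time.

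**4. Direction.** Understatement is usual but not guaranteed. Take a constructed example with recovery placed on the contact day. Arm A has 45%, 15% and 5% recovering at days 5, 10 and 15. Arm B has 40%, 35% and 15%.
- Recovered-only: A = (2.25 + 1.50 + 0.75)/0.65 = 6.9 days; B = (2.00 + 3.50 + 2.25)/0.90 = 8.6 days.
- Unrecovered patients counted at 15 days: A = 4.50 + 15 × 0.35 = 9.75; B = 7.75 + 15 × 0.10 = 9.25.

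The order of the arms reverses.

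**The case against.** The strongest reply is that the article defines a measure, not an estimator. It never says that unrecovered patients are dropped, and an analysis plan not shown could settle their handling. It is right that exclusion is an inference. But no plan can obtain the full mean from 15 days of follow-up without extrapolation, and entering unrecovered patients at 15 days gives a restricted mean, which is a different quantity from the one defined. The mismatch between quantity and horizon stands.

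The article does not support four stronger readings that a reader might infer:
- **Recovery is known only to the nearest five days.** Contacts are mainly phone calls, which can ask for the actual date, and the record form is not shown.
- **Patients whose respiratory illness worsens are withdrawn.** The discontinuation rule concerns worsening of the HIV clinical condition.
- **The outcome exists to show that withholding antibiotics is harmless.** No passage gives it that purpose, and no non-inferiority claim is attached to it.
- **Most of a delay is lost.** In the 8 vs 10 case the untruncated log-normal means differ by 2.39 and 2.75 days (log-SD 0.6 and 0.8), so the recovered-only difference is about 62% to 75% smaller. But 15 days of follow-up cannot estimate that mean. The restricted mean itself falls 40% to 56% short of it (1.44 against 2.39; 1.20 against 2.75).

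It is also fair that being on treatment is not the same as being symptomatic, that the continuation step applies to one branch only, and that the share of patients in that branch is unknown.

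**Conclusion.** The point holds for a secondary outcome and should be corrected. As defined, the mean cannot be observed for every patient. Averaging completed times selects on the outcome and will usually understate a difference between arms.

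Measured against what 15 days of follow-up can support, the shortfall is about 4% to 23% with medians of 4 to 6 days (log-SD 0.4 to 0.6), and about 37% to 44% with medians of 8 to 12 days (log-SD 0.6 to 0.8). These figures rest on assumed log-normal recovery, exact recovery dates within the window, and exclusion of unrecovered patients. If nearly everyone recovers by day 15, the effect is small.

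**What to change.** Replace the plain average with two measures:
1. The proportion completely recovered by t1, t2 and t3 among all enrolled patients, with those unrecovered at t3 counted as not recovered.
2. The restricted mean time to recovery over 15 days, with patients unrecovered at day 15 censored there. Use the reported recovery date where the calls record it, and interval censoring otherwise.

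Report patients discontinued because their HIV condition worsened separately, with a sensitivity analysis that counts them as not recovered. Counting them so in the main analysis would make a composite outcome, which is a choice and not a correction.

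The cost is a change of analysis wording and, if the form lacks it, one recovery-date field; no contacts are added. There are two limits. The result describes only the first 15 days and should be labelled so. Recruitment began in June 2024 and all sites are enrolling, so a date field added now would be missing for patients already enrolled; for them, interval censoring between contacts applies.
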